### 2.5. Participants

To be included in the project, participants will need to meet the following inclusion criteria:Aged between 18 and 66 years old.Women diagnosed with FM by a rheumatologist and meeting the more recent diagnostic criteria of the American College of Rheumatology [21]. Thus, (1) pain in at least 4 of 5 regions, (2) symptoms at a similar level for at least 3 months, and (3) widespread pain index (WPI) ≥ 7 and symptom severity scale (SSS) scores ≥ 5 or WPI of 4–6 and SSS score ≥ 9.Not suffering pathologies that contraindicate the exercise program or require special attention (coronary, thrombosis, bone, renal, moderate or severe pulmonary pathologies, etc.). The Physical Activity Readiness questionnaire (PAR-Q) for the practice of physical activity and sport [22] will be administered to control if anyone suffers any disease that impedes the physical load.Not suffering any pathology that requires the use of psychotropics or affects the vestibular system to avoid possible influences on balance measures.Not suffering any neurodegenerative pathology such as: Parkinson’s disease or multiple sclerosis.Returning the signed informed consent form of the study.Not being physically active as defined by the World Health Organization (WHO) during the previous 3 months.Trying to keep in the same FM association.Having the ability to walk and communicate on her own.Accessing to a device where video-conferences can be held.

### 2.6. Interventions

**Experimental group (Tele-SSE):** The experimental group will receive Tele-SSE training, 3 times a week, for 12 months. They will be given training guidelines through a brochure and all sessions will be tracked through video-conferencing on a mobile phone. Two to six patients will simultaneously perform the exercise in a common place, which will be a room or dependency yielded by each participating association with Internet connection via WIFI. SSE will be carried out on a 250 × 100 cm dimensioned thin carpet, divided into 40 squares of 25 × 25 cm. SSE includes a total of 200 different movement patterns that are classified, based on its difficulty, into three general levels: Beginner, intermediate, and advanced. The beginner level has two sublevels, while the intermediate and advanced levels have 3 sublevels. The proposed intervention will include a progression along with the different levels, which is shown in Table 1. Participants will start by movement patterns like walking and little by little they will make more complex patterns that will require multidirectional movements. Participants should not step on the squares dividing lines. The number of steps patterns and difficulty will monthly increase until the maximum level, where they will be maintained until the end of the intervention.

In all sessions, the SSE expert will phone the group of participants and will indicate the training to be done. Participants will have a brochure detailing the 200 movement patterns, which they can consult while the SSE expert indicates the sequence to follow during the class that day. Before starting the session, the first activity to be carried out will be to remember the last movement pattern executed in the previous session. Once the patients have memorized the pattern, which is expected to be achieved after 4–5 repetitions, based on a previous study [23], they will continue with the session autonomously. At the end of each session, they will contact the SSE expert who will ask them about the session development and will question them about two scales: The rating will be of perceived exertion [24] and level of pain, also recording any incident or problem during the training session.

**Control group:** The control group will continue with the treatment carried out within the public health system (usual care).

### 2.7. Measures and Procedures

A variety of tools will be used to assess the utility and effectiveness of the exercise program (Table 2).

#### 2.7.1. Randomized Trial Main Measures

**Applicability.** The percentage of participants with FM who can perform the proposed training. If any participant is unable to perform the intervention, the cause will be noted.

**Safety.** A record shall be kept about any incidence, injury or problem during the sessions, as well as if possible, the origin of the problem.

**Number of falls in the last year and six months.** Participants will be asked about the number of falls that they have suffered in the past year and six months. The World Health Organization (WHO) definition of falls will be adopted, namely: “Involuntary events that cause the body to lose its balance and find itself on land or on another firm surface that stops it”.

**Incremental cost-effectiveness ratio.** The average cost of the intervention and the effects on health will be calculated for both intervention and control groups. The measurement of health effects is defined as Quality Adjusted Life Years (QALYs), which is calculated by multiplying the life years (life expectancy) with the quality of life of the participants [25]. The health-related quality of life will be evaluated using the EQ-5D-5L questionnaire [26] and this measure will be used for sample calculation. Incremental cost-effectiveness ratio will be calculated by dividing the difference between the average costs of both groups by the difference in mean QALYs gained in both groups. The utilities needed to calculate the QALYs will be computed for each set of health status using the algorithm available on the official website of the EuroQol group (http://www.euroqol.org/). The algorithm used to calculate the EQ-5D-5L utility index will be the “crosswalking” of the EuroQol levels Spanish version. This utility index is comprised between −0.654 (corresponding to the worst state of health and equivalent to 55555) and 1 (perfect state of health and equivalent to 11111).

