## Abstract

Background: Women with fibromyalgia (FM) have 2.5 falls per year compared to the 0.5 falls in people without FM. This fact poses a significant health expense. Square Stepping Exercise (SSE) is a balance training system that has been shown to be effective in preventing falls in the elderly. However, there are neither studies in people with FM nor studies that apply SSE through video-conferencing (Tele-SSE). The objectives of this project are 1) to investigate the applicability, safety, decrease in the number of falls, and incremental cost-effectiveness ratio of prevention of falls program through Tele-SSE in women with FM, and 2) to study the transfer of obtained results to the public and private socio-health economy of Extremadura. Methods/Design: A randomized controlled trial with experimental (Tele-SSE) and control (usual treatment) groups will be carried out. The application of Tele-SSE will be performed for 12 months (three times per week) and one additional follow-up month after the intervention. A focus group including agents to identify key points to transfer the findings to the public and private sectors in Extremadura. One-hundred and eighteen women with FM will be recruited and randomly distributed into the two groups: Experimental (Tele-SSE; *n* = 59) and control group (Usual care; *n* = 59). Primary outcome measures will be: 1) Applicability; 2) safety; 3) annual number of falls; and 4) incremental cost-effectiveness ratio. Secondary outcomes will be: 1) Balance; 2) fear of falling; 3) socio-demographic and clinical information; 4) body composition; 5) physical fitness; 6) physical activity and sedentary behavior; 7) quality of life-related to health, mental health, and positive health; 8) pain; 9) disability level; 10) cognitive aspects; and 11) depressive symptoms. Regarding the focus group, the acceptability of the Tele-SSE will be evaluated in social-sanitary agents and will include Tele-SSE in their services offer. A statistical analysis will be carried out by treatment intention and protocol. In addition, a cost-effectiveness analysis from the perspective of the health system will be performed. Discussion: This project aims to improve the efficiency and equity of physical therapy services based on tele-exercise in preventing falls in people with FM. Furthermore, orientations will be given in order to transfer the obtained findings into the social-sanitary system and market.

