### 2.8. Statistical Analysis

Baseline characteristics of participants will be presented as the mean (standard deviation) for continuous variables and proportions for categorical variables. The normality will be checked using the Kolmogorov-Smirnov test. Then, two types of analyses will be performed: 1) An intention-to-treat analysis including all participants and 2) a per-protocol analysis using only those participants who complete the study.

**Intention-to-treat analysis.** This analysis will include all randomly assigned participants in their corresponding groups. Multiple imputations will be used to impute lost data. The effects of the intervention on the main and secondary variables will be computed using a repeated measures ANCOVA test, adjusted by age and baseline values. Results shall include the Cohen’s *d* effect size (95% confidence interval) and statistical significance for each dependent variable respect to time and its interaction effects (group × time). Statistical significance shall be established at the conventional level of *p* < 0.05. In sensitivity analyses, the data imputation will be made from the baseline patient data and from those participants who completed the study, in order to avoid estimation biases. 

**Analysis by protocol.** Similar analyses than those described above will be carried out, but only using participants who have attended at least 75% of the sessions.

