## Figures and Tables

**Table 1 ijerph-17-00695-t001:** Proposal progression of Tele-SSE training.

Month	Frequency (Days a Week)	Session Duration	Number of Steps per Sequence	Level of Difficulty
1	3	50 min	4	Beginner 1 and 2
2	3	50 min	6	Intermediate 1
3	3	50 min	6	Intermediate 2
4	3	50 min	8	Intermediate 3
5	3	50 min	8	Advanced 1
6	3	50 min	8	Advanced 2
7	3	50 min	8	Advanced 3
8	3	50 min	8	Advanced 3
9	3	50 min	8	Advanced 3
10	3	50 min	8	Advanced 3
11	3	50 min	8	Advanced 3
12	3	50 min	8	Advanced 3

**Table 2 ijerph-17-00695-t002:** Assessments schedule for both experimental and control group.

Assessment	Baseline	Month 3	Month 6	Month 9	Month 12	Month 13
Applicability	x				x	x
Safety	x				x	x
Number of falls in the last year and six months	x		x		x	x
Incremental cost-effectiveness ratio	x				x	x
Sociodemographic data	x					
Balance	x	x	x	x	x	x
Fall Risk	x	x	x	x	x	x
Fear of falling	x	x	x	x	x	x
Body composition	x	x	x	x	x	x
Physical condition	x	x	x	x	x	x
Pain	x	x	x	x	x	x
Health-related quality of life	x	x	x	x	x	x
Incapacity of fibromyalgia	x	x	x	x	x	x
Depression	x	x	x	x	x	x
Happiness	x	x	x	x	x	x
Physical activity and sedentary behaviors	x	x	x	x	x	x
Clinical global impression	x	x	x	x	x	x

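### Safety, a primary outcome, is defined only on Tele-SSE sessions, yet it is scheduled in both arms before, during and after the programme and falls under a baseline-adjusted ANCOVA

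*Protocol article*

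**What the plan says.** The Abstract lists the primary outcomes: "Primary outcome measures will be: 1) Applicability; 2) safety; 3) annual number of falls; and 4) incremental cost-effectiveness ratio".

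Section 2.7.1 defines the first two. For applicability: "The percentage of participants with FM who can perform the proposed training". For safety: "A record shall be kept about any incidence, injury or problem during the sessions", with the origin of the problem noted where possible.

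Section 2.6 shows how the safety record is made. At the end of each Tele-SSE session the women contact the SSE expert, who asks about exertion and pain, "also recording any incident or problem during the training session". The control group stays on usual care and has no sessions.

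Table 2 is titled "Assessments schedule for both experimental and control group". Its rows for applicability and safety carry the same marks: baseline, month 12 and month 13. According to the Abstract, the last of these is a follow-up month after the intervention.

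Section 2.8 states: "The effects of the intervention on the main and secondary variables will be computed using a repeated measures ANCOVA test, adjusted by age and baseline". Effects are to be reported for time and for group by time. It makes no exception for safety or applicability.

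**The concern.** The definition, the schedule and the analysis of safety do not fit together. Something recorded only in training sessions cannot be assessed in women who have none, nor at visits when nobody is training. Two of the four primary outcomes therefore cannot be analysed by the one model that section 2.8 gives for the main variables.

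For safety there is more at stake than the model. Section 4 looks ahead to what would follow if the programme proved effective and safe. A log of session incidents in one arm describes what happened in sessions. It does not show whether women assigned to Tele-SSE had more injuries or other adverse events overall than women on usual care. The randomised comparison that could show this needs events asked about in the same way in both arms. A later analysis plan can choose a different model, but it cannot recover events that nobody asked about during follow-up.

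**Working it through.** **Sample size, for reference.** Section 2.3 gives a difference of 0.15, an SD of 0.26, two-sided alpha 0.05, power 0.80 and 20% loss.
- n per arm = 2 × (0.26 × (1.960 + 0.842) / 0.15)² = 47.16.
- 47.16 / 0.80 = 58.95, so 59 per arm and 118 in total, as stated.

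This figure rests on EQ-5D-5L and has no bearing on safety or applicability.

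**Where safety can take a value as defined.**

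| | Baseline | Months 1–12 | Month 13 |
|---|---|---|---|
| Tele-SSE | no sessions yet | sessions, incidents recorded | programme ended |
| Usual care | no sessions | no sessions | no sessions |
| Table 2 mark, both groups | yes | month 12 | yes |

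Of the six arm-by-visit cells that Table 2 marks (two arms, three visits), only the Tele-SSE cell at month 12 can hold a value.

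**Planned exposure.** Three sessions a week (section 2.6) over 52 weeks is 3 × 52 = 156 sessions per woman. For 59 women this is 156 × 59 = 9,204 sessions, assuming full attendance. In the control arm it is 0.

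**Can the stated model be fitted?** Take a single post-baseline time with four columns: intercept, group, age and baseline.
- If baseline is set to 0 for everyone, that column carries no information and the design matrix has rank 3 of 4. No baseline adjustment is possible.
- If control values are treated as absent, only the Tele-SSE rows remain. The group column equals the intercept, the rank is 2 of 4, and no group effect can be estimated.
- If controls are coded 0, a group coefficient can be computed, but it compares incidents over about 9,204 sessions with incidents over none. That is not a safety comparison.
- Multiple imputation, which section 2.8 plans for lost data, does not help. The control values are not lost; under the definition they do not exist.

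**What harm-related data both arms do have.**
- Falls: asked of all participants with no restriction to sessions (section 2.7.1), at baseline and months 6, 12 and 13 (Table 2).
- Pain: measured in both groups at baseline and at months 3, 6, 9, 12 and 13 (Table 2), and also before and after each training (section 2.7.3, Pain).
- Medication, primary care visits and hospital admissions: costed (section 2.9), with average costs calculated for both groups (section 2.7.1).

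None of these is defined as safety. What remains without a defined collection is non-fall injuries and other adverse events outside sessions, in either arm.

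**Applicability.** This is the share of women able to do the training, which is a single percentage in the trained arm. It needs no comparator. Its faults are the control-arm, baseline and month-13 marks in Table 2 and its inclusion, as a main measure, in the ANCOVA sentence.

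**The case against.** The strongest reply is that the literal reading was never meant. The incremental cost-effectiveness ratio is also a main measure, yet section 2.9 analyses it separately, so the ANCOVA sentence is not exhaustive. An incident log and a group percentage have no Cohen's d. Table 2 is loosely marked elsewhere too: the clinical global impression, which measures improvement due to the intervention, carries a baseline mark. Descriptive reporting of such outcomes may well be in an analysis plan that is not shown. This stands in part. It makes the ANCOVA and table faults a matter of clarification, but it does not supply a definition of safety that works in the control arm.

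Three stronger readings are tempting, and the document does not support them.
- A reader might infer that falls or pain flares outside sessions go unrecorded. They do not: both are measured in both arms, and falls are themselves a primary outcome. For the same reason, the high background fall rate does not measure the gap, because falls are the harm with an explicit randomised comparator.
- A reader might infer that no adverse event is collected in controls. Table 2 does schedule safety for that arm. The text is contradictory and leaves undefined what would be recorded there; it does not establish that nothing is.
- A reader might infer that applicability lacks a control. It does not need one.

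Two further points are fair. The remark on safety in section 4 is conditional, not a planned between-arm claim. And new questions put by blinded assessors could reveal allocation if women mention their sessions. The remedy has to deal with that.

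**Conclusion.** The point holds in a limited form. Safety as defined exists only for Tele-SSE sessions, while Table 2 and section 2.8 treat it as a both-arm, baseline-adjusted outcome. These passages must be reconciled. The substantive gap is non-fall injuries and other adverse events outside sessions, which have no defined collection in either arm; falls, pain and care use are covered but are not designated as safety. For applicability only the table marks and the analysis sentence are wrong.

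The change should be made because a control-arm record can only be obtained prospectively. It does not threaten the falls comparison, the cost-utility analysis or the sample size. The size of the gap cannot be put as a number of events, since the document gives no rate for non-fall injuries or other adverse events. The conclusion rests on reading the article as it stands; the full protocol may define more. The session count assumes 52 weeks and full attendance.

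**What to change.** 1. In section 2.7.1 and Table 2, add injuries and adverse events to safety, asked with the same question in both arms at the existing post-baseline visits (months 3, 6, 9, 12 and 13). Use a self-completed form so that blinded assessors do not learn the allocation. Compare rates per woman-year with a 95% confidence interval, and read them alongside the between-arm falls comparison. The trial was not sized for this, so it is estimation, not a powered test.
2. Report session incidents separately, as a descriptive rate per session in the Tele-SSE arm.
3. Report applicability as a proportion of all women randomised to Tele-SSE, with an exact 95% confidence interval, and remove its baseline, month-13 and control-arm marks from Table 2. As a guide to precision, if 80% of 59 women can do the training (an assumed value), the approximate half-width is 1.96 × √(0.8 × 0.2 / 59) = 0.102, or about 10 points.
4. In section 2.8, state that safety and applicability are excluded from the ANCOVA sentence.

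The cost is one short form at visits that already take place, an edit to Table 2 and a sentence or two in section 2.8. There are no extra visits and no change in sample size. The downsides are slightly more data to collect and some remaining risk of unblinding, which the self-completed form keeps small.

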### 2.4. Randomization and Blinding

After baseline assessments, all participants will be randomly assigned to two groups: Experimental (Tele-SSE) or control (usual care). A simple computer-generated randomization sequence will be created before participants are enrolled (1:1) using the computer software Research Randomizer (Version 4.0, Geoffrey C. Urbaniak and Scott Plous, Middletown, CT, USA) (http://www.randomizer.org). The randomization sequence will be made by a member of the research team without clinical participation in the trial. The assignment will be hidden in a password-protected computer file. Although participants will know their group assignment, outcome evaluators and data analysts will be blinded to the assignment.

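### Falls recall windows cross randomisation at month 6 and the end of the intervention at month 13, so the follow-up month cannot be measured; the month 12 annual count is sound

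*Protocol article*

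**What the plan says.** The Abstract lists "annual number of falls" among four primary outcomes. Section 2.7.1 gives the method of collection: "Participants will be asked about the number of falls that they have suffered in the past year and six months". Table 2 repeats this in the row "Number of falls in the last year and six months", marked at baseline and months 6, 12 and 13. Visits also take place at months 3 and 9, but falls are not asked about there.

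The time axis comes from two other places. Section 2.4 puts randomisation after baseline: "After baseline assessments, all participants will be randomly assigned to two groups". The Abstract gives the duration: "The application of Tele-SSE will be performed for 12 months (three times per week) and one additional follow-up month after the intervention".

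Section 2.8 states that effects on main and secondary variables will be "computed using a repeated measures ANCOVA test, adjusted by age and baseline values", with time and group-by-time effects reported. It does not say which recall window, or which visits, supply the falls values.

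**The concern.** A recall window is useful when it starts and ends at the events that define the comparison, here randomisation and the end of the intervention. Some of these windows straddle one of those points. A total that includes falls before randomisation carries months in which the arms cannot differ because of treatment. A total taken one month after the intervention, but reaching back six or twelve months, mostly repeats falls already reported at month 12.

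If such totals enter the repeated measures model, the time pattern and the group-by-time effect partly reflect the windows and not the intervention. The follow-up month would also yield no usable falls result. The literal wording adds a further risk, since the question can be taken as one window of 18 months.

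Participants know their group (Sections 2.1 and 2.4), so blinded assessors do not protect a self-reported count. Long recall leaves more room for error.

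**Working it through.** **Plan's own figure.** The article states no expected reduction in falls, so there is no falls figure to reproduce. The sample size rests on EQ-5D-5L (Section 2.3): 2 × (1.96 + 0.84)² × 0.26² / 0.15² = 47.16 per arm using unrounded normal quantiles. Then 47.16 / 0.80 = 58.95, so 59 per arm and 118 in total. It reproduces and is not affected by this point.

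**Inputs.** Randomisation at month 0, intervention in months 0 to 12, follow-up to month 13, falls asked at months 6, 12 and 13. The control rate is 2.5 falls per year (Background). The true on-intervention rate ratio of 0.70 is an assumption; 0.5 to 0.8 is shown as a range.

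**Formula.** Split each window of L months into months before randomisation (pre), on intervention (on) and after it (post). The apparent ratio is (pre + on × RR + post × RR_post) / L, where RR_post is RR if the benefit persists and 1 if it vanishes at month 12.

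| Visit, window | pre / on / post (months) | Apparent ratio if true ratio is 0.70 |
|---|---|---|
| Month 6, 6 months | 0 / 6 / 0 | 0.70 |
| Month 6, 12 months | 6 / 6 / 0 | (6 + 4.2) / 12 = 0.85 |
| Month 12, 6 months | 0 / 6 / 0 | 0.70 |
| Month 12, 12 months | 0 / 12 / 0 | 0.70 |
| Month 13, 6 months | 0 / 5 / 1 | 0.70 if it persists; (3.5 + 1) / 6 = 0.75 if it vanishes |
| Month 13, 12 months | 0 / 11 / 1 | 0.70 if it persists; (7.7 + 1) / 12 = 0.725 if it vanishes |

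For true ratios from 0.5 to 0.8, the month 6 past-year count shows 0.75 to 0.90, always half the relative reduction.

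**Effect on the time pattern.** At 2.5 falls per year, the expected group difference in past-year counts is 2.5 − 2.125 = 0.375 at month 6 and 2.5 − 1.75 = 0.75 at month 12. A constant effect from day one would seem to double. The 0.375 is correct as the number of falls averted in six months, and the six-month window gives the same 0.375 (1.25 − 0.875). It misleads when read as an annual figure beside month 12. Six-month counts give 0.375 at both visits.

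**Overlap with the covariate.** The baseline past-year count covers months −12 to 0 and the month 6 past-year count covers −6 to +6. Six months of the same falls sit in both covariate and outcome.

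**Can the follow-up month be recovered?** Let a, b, c, d and e be the falls in months 0–1, 1–6, 6–7, 7–12 and 12–13. The clean totals are a + b (month 6) and c + d and a + b + c + d (month 12). Month 13 adds d + e and b + c + d + e. To obtain e alone by adding and subtracting, a must cancel, which rules out a + b; then b must cancel, which rules out b + c + d + e; then c must cancel, which rules out c + d. Only d + e is left, and d cannot be removed. The month 6 past-year total, less the baseline six-month total, only gives a + b again.

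**18-month reading.** Month 6 is 12 / 6 / 0, giving (12 + 4.2) / 18 = 0.90. Month 12 is 6 / 12 / 0, giving (6 + 8.4) / 18 = 0.80. Month 13 is 5 / 12 / 1, giving 0.78 if the effect persists and 0.80 if it vanishes.

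**The case against.** The strongest reply is that the named outcome is not contaminated. With two windows, the past-year count at month 12 runs exactly from randomisation to the end of the intervention and is the annual number that the Abstract names. The six-month count at month 6 is equally clean, and collecting both lengths fits a plan to use six months at month 6 and a year at month 12. This stands. A reader might infer that the primary falls result is diluted, or that the mixed values each combine falls before, during and after the intervention. The documents do not support either. On the two-window reading no value spans all three periods, and month 13 holds no pre-randomisation falls.

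Second, Section 2.8 is one general sentence for many variables, and the choice of window may sit in an analysis plan that is not shown. This stands in part. The article does not say that the mixed windows enter the model; it only does not exclude them. But no analysis plan can recover falls in months 12 to 13 from the questions asked.

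Third, the 18-month reading is strained, since the Abstract says annual and the visits at months 6 and 12 match the two lengths. Agreed: it calls for clearer wording and does not show that 18 months was meant.

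Fourth, month 13 dilution is at most one sixth of the reduction, and nil if the benefit lasts the month. This also stands. The stronger complaint about month 13 is that the windows cannot tell these two cases apart.

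**Conclusion.** The point holds as a moderate fault in data collection that is cheap to correct. It is not a defect in the annual count at month 12. The established parts follow from the visit schedule alone: the month 6 past-year count is half pre-randomisation, and neither month 13 window isolates the follow-up month. The sizes given (0.85 at month 6; up to 0.75 or 0.725 at month 13) assume a true rate ratio of 0.70 acting from day one. The distortion of the time and group-by-time effects is conditional on the mixed windows entering the model. Recall error and reporting bias are plausible with unblinded self-report, but the article gives nothing from which to size them.

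**What to change.** - Name falls from randomisation to month 12 as the primary falls outcome.
- Ask about falls since the last visit at months 3, 6, 9, 12 and 13. The first four answers add up to months 0 to 12, and month 13 covers only months 12 to 13.
- Use the 12-month pre-baseline count only as a covariate.
- Reword the recall question so that it cannot be taken as one 18-month period.

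The cost is one reworded question and two more marks in Table 2, at visits that already take place. Recall shortens to three months or less between attended visits, and a woman lost after month 9 contributes falls to month 9 instead of month 6.

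Two limits remain. The count is still unblinded self-report. The follow-up month will also be thin: at 2.5 falls per year, 59 control women would have about 59 × 2.5 / 12 = 12 falls, so that result is descriptive.

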### 2.9. Cost-Effectiveness Analysis

A cost-utility analysis will be conducted with a health system perspective in line with the methodological recommendations of health economists [70], and the guidelines defined in the scientific literature [18].

The study will be carried out considering the costs and health effects of the intervention, including the effect of Tele-SSE on the number of falls. Only the direct costs of the program (i.e. medication, primary care visits, and hospital admissions) will be considered. Likewise, the salaries of the person hired to carry out the video-conferences will be considered in agreement with the set-out guidelines, based on the corresponding collective agreement. It will also include the costs of the essential material for the Tele-SSE implementation, such as training mats, mobile phones, and Internet connection.

First, the average costs and effectiveness will be calculated for each group, i.e., the Quality Adjusted Life Years (QALYs) earned. Subsequently, the incremental cost-effectiveness ratio will be calculated [71] and various sensitivity analyses will be conducted, including probabilistic, which will be carried out with 1000 repetitions [72]. These replicas will be included in the cost-effectiveness plan and will be used to make the acceptability curve. Then, we will be able to see in which quadrant of the cost-effectiveness plan the Tele-SSE intervention is located, which will indicate whether the Tele-SSE has been costly and effective than the intervention made by the control group (usual care).

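### The primary ICER defines QALYs as life expectancy times quality of life; followed literally against about 12 months of costs, this inflates the QALY difference roughly 20- to 80-fold

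*Protocol article*

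**What the plan says.** The Abstract makes the ICER a primary outcome: "Primary outcome measures will be: 1) Applicability; 2) safety; 3) annual number of falls; and 4) incremental cost-effectiveness ratio".

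Section 2.7.1 sets out how it is built. The health effect is the QALY, "which is calculated by multiplying the life years (life expectancy) with the quality of life of the participants". The instrument is fixed: "The health-related quality of life will be evaluated using the EQ-5D-5L questionnaire". The ratio is obtained by "dividing the difference between the average costs of both groups by the difference in mean QALYs gained in both groups". No other section gives a different way to calculate a QALY; section 2.9 only refers to QALYs earned in each group.

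On timing, the Abstract says the intervention "will be performed for 12 months (three times per week) and one additional follow-up month after the intervention". In Table 2 the row "Incremental cost-effectiveness ratio" is marked at baseline, month 12 and month 13. The health-related quality of life row is marked at all six visits, but section 2.7.3 lists 15-D, SF-12 and HUIv3 under that heading, not EQ-5D-5L.

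On costs, section 2.9 takes a health system perspective and then states: "Only the direct costs of the program (i.e. medication, primary care visits, and hospital admissions) will be considered". It adds the salary of the person running the video-conferences, and: "It will also include the costs of the essential material for the Tele-SSE implementation, such as training mats, mobile phones, and Internet connection". It states no time horizon for costs.

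**The concern.** A QALY difference and a cost difference can be divided by each other only if they cover the same period. The stated rule multiplies utility by life expectancy, while every cost item described belongs to running the programme or to care used by participants, with no projection beyond the trial. Applied literally, the rule also carries a utility difference seen for 12 to 13 months over the rest of life without saying so.

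The error would favour the intervention: too many QALYs in the denominator make the ICER look too small, and the cost-effectiveness plane and acceptability curve inherit this. The Discussion says that decision-makers would be urged to adopt Tele-SSE if it proves cost-effective, so the definition matters beyond the paper.

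A second, smaller issue is how often EQ-5D-5L is measured. Once the definition is corrected to a within-trial area under the curve, the result depends on how many points the curve has.

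**Working it through.** **Inputs from the protocol article**
- Utility difference 0.15, SD 0.26, two-sided alpha 0.05, beta 0.2, loss to follow-up 20% (section 2.3)
- Intervention 12 months plus one month of follow-up (Abstract)
- Eligible age 18 to 66 years (section 2.5)
- Visits at baseline and months 3, 6, 9, 12 and 13 (Table 2)

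**Assumptions, not in the document**
- Remaining life expectancy L, shown at 10, 20, 40 and 65 years
- Discounting at 3% a year, as a sensitivity check

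**Step 1. The plan's own figure.** Per arm, 2 × (0.26 × (1.960 + 0.842) / 0.15)² = 47.16. Allowing for 20% loss, 47.16 / 0.80 = 58.95, so 59 per arm and 118 in total. The stated size reproduces, so 0.15 is a fair utility difference to carry forward.

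**Step 2. QALY difference within 12 months.**
- Linear growth from 0 at baseline to 0.15 at month 12: 0.5 × 0.15 × 1 = 0.075
- Full effect from the start: 0.15 × 1 = 0.15

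**Step 3. QALY difference under the stated rule: L × 0.15.** The ratio is taken against 0.15 (lower end) and 0.075 (upper end).

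| L (assumed) | Rule gives | Inflation, undiscounted | Inflation, 3% discounted |
|---|---|---|---|
| 10 years | 1.5 | 10–20× | 9–18× |
| 20 years | 3.0 | 20–40× | 15–31× |
| 40 years | 6.0 | 40–80× | 24–48× |
| 65 years | 9.75 | 65–130× | 29–59× |

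For example, 3.0 / 0.15 = 20 and 6.0 / 0.075 = 80. With the cost difference unchanged, the ICER is divided by the same factor.

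**Step 4. The EQ-5D-5L schedule, as a separate matter.** With baseline and month 12 only, the trapezoid always gives 0.075 when the month-12 difference is 0.15. With visits at 0, 3, 6, 9 and 12 months:

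| Course of the effect | Five-point curve | Two-point curve | Error of two points |
|---|---|---|---|
| Full by month 3, then flat | 0.15 × (0.125 + 0.75) = 0.131 | 0.075 | 1 − 0.075/0.131 = 43% too low |
| Linear to month 12 | 0.075 | 0.075 | none |
| Nothing until month 9, 0.15 at month 12 | 0.5 × 0.15 × 0.25 = 0.019 | 0.075 | 0.075/0.019 = 4× too high |

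**The case against.** The strongest defence is that the sentence on life years carries a citation and may be only a textbook description of a QALY. The ICER formula speaks of QALYs gained, section 2.9 speaks of QALYs earned, and both fit a within-trial calculation. The absence of a life table, extrapolation model or discount rate also suggests that no lifetime analysis was intended, and an article may leave such detail to a fuller document. This makes the size of the error conditional. It does not rescue the sentence, which is given as the definition for a primary outcome and is the only calculation stated.

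The cost horizon is not stated either. That costs run for about one year is the natural reading of the items listed, but it is an inference. If costs were also projected over life, the mismatch would shrink or vanish, though the unstated lifetime persistence of a 12- to 13-month utility difference would remain.

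On the schedule, section 2.7.1 names EQ-5D-5L as the measure of health-related quality of life, and the Table 2 row with that label runs at every visit. The omission in section 2.7.3 may be a labelling slip. In addition, 15-D and the SF-6D index from SF-12 would give intermediate utilities for a sensitivity analysis. Full benefit by month 3 is only one scenario: Table 1 raises the difficulty level until month 7.

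Two stronger readings are tempting. A reader might infer that the sparse schedule contributes to the order-of-magnitude error. It does not: it can push the result either way, or leave it unbiased. A reader might also infer that the cost list leaves out much of the saving from falls, citing about 148 control-arm falls a year (59 × 2.5 = 147.5). That number counts neither falls averted nor falls needing care, and the article gives no share of falls leading to emergency, imaging or specialist contacts. Omitting fall-related savings would also make the ICER less favourable, the opposite direction to the main point.

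**Conclusion.** The point holds in conditional form. The stated QALY rule does not fit a trial that observes utility for 12 to 13 months and describes no lifetime projection. If it is followed with about 12 months of costs, the QALY difference is inflated about 20 to 80 times over an assumed 20 to 40 remaining years (15 to 48 times at an assumed 3% discount rate), and the ICER falls by the same factor. Tenfold inflation needs only about 10 remaining years even against the full-effect figure of 0.15, without discounting.

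A reader might conclude that the reported ICER will certainly be wrong by this much. The article does not support that: it depends on a literal reading, an inferred cost horizon and an assumed life expectancy.

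The EQ-5D-5L schedule is a separate and smaller matter, itself inferred from sections 2.7.1 and 2.7.3 and Table 2. Two points could be 43% too low, right, or 4 times too high, depending on when the effect appears. The cost list is a minor inconsistency with the stated perspective, of unknown size.

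The definition should be corrected before analysis, because it governs a primary outcome.

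**What to change.** - In sections 2.7.1 and 2.9, define QALYs as the area under the EQ-5D-5L utility curve from baseline to month 12, and adjust the between-arm difference for baseline utility.
- State the same 12-month horizon for costs. Label any lifetime extrapolation a scenario, with its persistence assumption and discount rate given.
- In Table 2, list EQ-5D-5L by name, including months 3, 6 and 9.
- As a minor edit, reconcile the restrictive cost list in section 2.9 with the health system perspective, either by widening the list or by saying why it is limited.

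The cost is a few revised sentences and one five-item questionnaire at three visits that already take place. The extra measurements have to be collected during the trial; an analysis plan written later cannot recover them.
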